### Aims or Hypotheses

This RCT is testing a heuristics-based intervention designed to enhance symptom self-management in AYAs with cancer. Primary aim 1 is to determine the effects of the C-SCAT versus usual care on the primary outcomes of self-efficacy for symptom management and symptom self-management behaviors immediately postintervention (time 1) and at follow-up 1 month later (time 2). Aim 1 hypotheses are that AYAs using the C-SCAT will have higher self-efficacy for symptom self-management and higher scores on symptom self-management behaviors compared to AYAs receiving usual care. Primary aim 2 is to examine the effects of the C-SCAT versus usual care on secondary outcomes (eg, symptom severity, symptom distress, social function, and satisfaction with social function) immediately postintervention (time 1) and at follow-up 1 month later (time 2). Aim 2 hypotheses are that AYAs using the C-SCAT will have lower symptom distress and symptom severity and higher social function and satisfaction with social function compared to AYAs receiving usual care.

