#### Aims

Aim 1 is to determine the effects of the C-SCAT versus usual care on the primary outcomes of self-efficacy for symptom management and symptom self-management behaviors immediately postintervention (time 1) and at follow-up 1 month later (time 2). Self-efficacy for symptom management and symptom self-management behaviors will be assessed at times 0, 1, and 2 and will be compared between the C-SCAT intervention group and the UCCG. We anticipate using a linear mixed effects model to test the effect of the C-SCAT versus usual care. The general form of the mixed linear model [52-54] is given by y=XB+ZU+ e, where y is the observed data vector (PROMIS S-E and SSMBT), X is a known design matrix, B is a vector of unknown fixed effects, Z is a known design matrix, U is a vector of unknown random effects, and e is a vector of unknown random errors. This model will include a random effect for participant (represented by ZU in the equation) and fixed effects for group (C-SCAT and UCCG), time (0, 1, and 2), group-by-time interaction, site (1, 2, 3, 4, and 5), group-by-site interaction, and population (adolescent and young adult; represented by XB in the equation). The model is flexible enough to accommodate the potential cofactors of race (eg, Black and White), ethnicity (eg, Hispanic and non-Hispanic), and gender (eg, male and female). The first step in testing aim 1 will be to test each of the primary variables (PROMIS S-E and SSMBT) using a contrast on the group-by-time interaction to specifically test for an immediate effect of C-SCAT versus the UCCG at time 1. A Bonferroni correction (*α*=.05/2=.025) is planned to adjust for testing each of the 2 primary variables. All other tests, for example, testing for a sustained effect at time 2, are considered supportive and will be testing with an *α* of .05. Modeling assumptions such as normality and homoscedasticity will be checked for each model. In the case of positively skewed data, a transformation (such as a log transformation) will be used to normalize the data. It is anticipated that all analyses will be performed using JMP (JMP 18, 2025 JMP 18; JMP Statistical Discovery LLC [55]) and SAS/STAT (Statistical Analysis Software Institute [56]) software, specifically PROC MIXED.

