Aim 2 is to examine the effects of the C-SCAT versus usual care on secondary outcomes (symptom severity, symptom distress, quality of life related to social function, and satisfaction with social function) immediately postintervention (time 1) and at follow-up 1 month later (time 2). The mixed effects linear model presented in the aim 1 analysis plan is anticipated to be sufficient for the analysis of the secondary outcomes in aim 2. The secondary outcomes are considered supportive of the tests of an immediate effect (aim 1) and will be tested with an *α*= of .05.

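### The Bonferroni split at time 1 is valid but Holm would do better at no cost in error rate, and the plan should state that Aim 1 is judged at time 1, because Aim 1 also names an ungated time 2.

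*Protocol article*

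**What the plan says.** Under Aims in the Data Analysis Plan, the first step for Aim 1 is a contrast on the group-by-time interaction for each primary outcome (PROMIS S-E and SSMBT), "to specifically test for an immediate effect of C-SCAT versus the UCCG at time 1". A Bonferroni correction, .05/2 = .025, "is planned to adjust for testing each of the 2 primary variables". The plan continues: "All other tests, for example, testing for a sustained effect at time 2, are considered supportive", each tested at .05. No order or condition links a time-2 test to the time-1 result for the same outcome.

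The Aims or Hypotheses section words Aim 1 more broadly. It concerns effects on both primary outcomes "immediately postintervention (time 1) and at follow-up 1 month later (time 2"), and the directional hypotheses that follow are not limited to time 1. The restatement of Aim 1 in the Data Analysis Plan names the same two time points.

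On Aim 2, the plan says "The secondary outcomes are considered supportive of the tests of an immediate effect (aim 1"), also at .05. Sample Size and Power uses the Bonferroni level of .025 with 90% power.

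**The concern.** There are two separate matters.

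The first is efficiency. Plain Bonferroni holds each outcome to .025 even when the other has already succeeded. Holm rejects whenever Bonferroni does, sometimes rejects more, and has the same familywise error. The Aim 1 hypotheses predict improvement on both outcomes, so the chance of winning on both matters, and that is where Bonferroni gives up most.

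The second is the scope of the claim. Aim 1 names two outcomes at two times, which makes four tests, and error is controlled for two of them. The same outcome faces a looser threshold at follow-up (.05) than at time 1 (.025). With p = .04 at both times, an outcome would miss at time 1 and pass at time 2. If that were then read as support for Aim 1, a sustained effect would be claimed where no immediate effect had been shown.

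**Working it through.** **Inputs from the article.** Alpha .025 per outcome at time 1 and .05 at time 2; differences of 10 and 4.8; residual standard deviations (called SE there) of 12.73 and 6.35; 99 completers.

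**Assumptions.** Two-sided tests and 1:1 allocation, neither of which is stated. The correlations between outcomes and between times are not given either, so ranges are used.

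**1. The plan's own figure.** .05/2 = .025, and .025 + .025 = .05. Under independence the time-1 family error is 1 − .975² = .049. Simulation with outcome correlations from 0 to .7 gives 4.3% to 5.0%. The declared family is controlled.

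**2. All four Aim 1 tests counted as one family.** The upper bound is .025 + .025 + .05 + .05 = .15. If independent, the error is 1 − .975² × .95² = .142. Simulation of four correlated two-sided z tests (1,000,000 draws per setting) gives:

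| Correlation between times | Correlation between outcomes | At least one false positive |
|---|---|---|
| 0 | 0 | 14.2% |
| .5 | .3 | 13.0% |
| .7 | .3 | 12.2% |
| .8 | .7 | 10.1% |

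**3. Holm against Bonferroni at 90% power per outcome.** The expected z is 2.241 + 1.282 = 3.523, so power at .05 is Φ(3.523 − 1.960) = .941. With independent outcomes:
- Per outcome under Holm: .900 + (.941 − .900) × .900 = .937.
- Both outcomes: Bonferroni .900² = .810; Holm .941² − .041² = .884.

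With an outcome correlation of .3, simulation gives per-outcome power .900 to .933 and both outcomes .821 to .888. The chance of at least one success is the same under both methods (.978). Under the null, Holm and Bonferroni have identical familywise error (.048 at correlation .3).

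**4. The same comparison with 99 completers.** Power per outcome is Φ(δ / (σ√(4/N)) − 2.241).
- PROMIS S-E: 10 / (12.73 × .2010) = 3.908, so power is Φ(1.667) = .952.
- SSMBT: 4.8 / (6.35 × .2010) = 3.761, so power is Φ(1.519) = .936.

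Results at outcome correlation .3, from Bonferroni to Holm:

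| True effect | PROMIS S-E | SSMBT | Both |
|---|---|---|---|
| As planned | .952 to .971 | .936 to .961 | .896 to .940 |
| 80% of planned | .811 to .856 | .780 to .834 | .660 to .759 |

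**5. Which gates keep .05.** Testing each outcome's time 2 at .025 only after its own Bonferroni rejection at time 1 gave a four-test error of 4.3% to 5.0% over the settings in step 2. Combining full Holm with that per-outcome gate does not hold. Suppose outcome A truly works at time 1 but not at time 2, and B does not work at time 1. Once A is rejected, B is tested at .05 and A's time 2 at .025. The error is then up to 1 − .95 × .975 = .074 if independent, with a bound of .075. Holm has already passed A's alpha to B, so none remains for A's time 2.

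**The case against.** The strongest reply is that the plan has already answered the scope question. It names a confirmatory family of two time-1 contrasts, controls it, and labels everything else supportive. Its Aim 2 paragraph identifies the Aim 1 tests with the immediate effect, and a sustained effect presupposes an immediate one. Prespecifying a controlled primary family and testing supportive endpoints at a nominal .05 is ordinary practice. Formal gating may also sit in a full analysis plan that is not shown.

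Most of this stands. A reader might infer that Aim 1 carries an error rate of 12-14%. The document does not support that: the four-test figure applies only if a time-2 result alone may establish Aim 1, which the analysis text does not say. The range also rests on assumed correlations and drops to about 10% when they are strong. A reader might also infer that the trial loses planned power. It does not, because the calculation already uses .025; the loss is only relative to Holm.

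What remains is that the wording of Aim 1 covers both time points without limit, so the supportive label and the aim do not quite match. The label alone does not stop a time-2 result from being read as support for Aim 1. On Holm, the reply is that Bonferroni is valid and the gain at 99 completers is modest. Both are true, but the gain costs nothing in error rate.

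The heading given to Aim 2 ("Primary aim 2 is to examine the effects of the C-SCAT versus usual care on secondary outcomes") is a labelling slip. The Abstract calls it the secondary aim, and no alpha depends on it.

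**Conclusion.** The time-1 rule is valid, with familywise error of at most 5%. It is less efficient than Holm by about 3 points of power per outcome and 7 points for both outcomes, at 90% power and correlation .3. With 99 completers and the planned effects, the difference is about 2 to 3 points per outcome and 4 points for both. It is larger if the true effects are smaller than planned: about 10 points for both at 80% of the planned effects.

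The scope of Aim 1 needs one clarifying sentence. Without it, a claim resting on time 2 alone would belong to a set of four tests with roughly a 10-14% chance of at least one false positive (bound 15%). That range assumes two-sided tests and between-time and between-outcome correlations up to .8 and .7.

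**What to change.** - Replace Bonferroni by Holm for the two time-1 contrasts: the smaller p-value at .025 and, if rejected, the other at .05. The sample size can stay as it is.
- State that Aim 1 is judged on the time-1 contrasts, and report time-2 results as supportive estimates with 95% confidence intervals.
- If a confirmatory time-2 claim is wanted, choose one of two routes. Either test time 2, again by Holm, only after both time-1 tests are rejected; or keep Bonferroni and test each outcome's time 2 at .025 after its own time-1 rejection. Do not combine full Holm with the per-outcome .025 gate.
- As a clerical matter, call Aim 2 secondary throughout.

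The cost is analysis-plan wording. The downsides are that simultaneous confidence intervals under Holm are less simple than under Bonferroni, and that no confirmatory time-2 claim is available unless the gate is passed.

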#### Missing Data

In addition to strategies to prevent missing data, such as completion checks after study visits and reminders, we will monitor for patterns of missing data when data are merged on a quarterly schedule and determine reasons for missing data. We will use mean imputation for any missing data within a scale. Following an intention-to-treat principle, participants with any postintervention data will be included in the analysis.

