### Trial Design

This study uses a multisite 2-group RCT design to evaluate the effects of the C-SCAT for improving symptom self-management versus usual care in AYAs who are within the first 3 months of a cancer diagnosis and who are receiving cancer treatment. For this study, cancer treatment is defined as a prescribed infusion (eg, chemotherapy or immunotherapy). Data collection occurs at 3 time points (times 0, 1, and 2). Time 0 (baseline, followed by randomization) occurs at or near the enrollment visit. The C-SCAT intervention period is approximately 12 weeks, depending on the participant’s treatment schedule. Time 1 (postintervention) occurs approximately 2 weeks (±7 d) after completion of the intervention. Time 2 (follow-up) occurs approximately 4 weeks (±7 d) after time as seen in Figure 2.

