### Data Collection

Data collection occurs at 3 time points (times 0, 1, and 2) at scheduled inpatient or outpatient visits (Figure 2). Baseline measures are collected at time 0, postintervention measures at time 1, and follow-up measures at time 2. Participants complete measures on a study-dedicated tablet computer using REDCap, or via a link to REDCap that is emailed to them. Study staff obtain clinical data from the electronic health record. The time 1 visit for the C-SCAT group is scheduled 2 weeks±7 days (to accommodate schedule changes) after completion of the intervention to allow time for the participant to have been at home (or outside the clinical setting) to self-manage their symptoms following chemotherapy. The time 1 visit for the UCCG group is scheduled 2 weeks±7 days (to accommodate schedule changes) after completion of the attention control visits. For both groups, the time 1 visit occurs during a scheduled inpatient or outpatient visit. Participants who are not scheduled for an inpatient or outpatient visit during the ±7-day window are contacted via telephone to complete the study measures and are sent a REDCap link via email. For both groups, the time 2 visit is scheduled 4 weeks±7 days from Time 1, and the same procedures for data collection as described earlier for time 1 are used.

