#### Sample Size and Power

A mixed effects linear model is planned to test for group differences across time for aims 1 and 2. The co-primary outcome variables from aim 1 are the PROMIS S-E and the SSMBT. From the outset, we planned to take a more conservative approach to the power analysis due in part to the limited number of SSMBT samples observed from only one site. Thus, for both primary variables, power was estimated using a 20% inflated variance estimate and a target power of 90% (as opposed to the usual 10% inflated variance and 80% power). A 20% inflated estimate of the residual SE was estimated as 12.73 for PROMIS S-E and 6.35 for SSMBT. Assuming the smallest clinically significant difference between the groups of 10 for PROMIS S-E and 4.8 for SSMBT, a Bonferroni adjusted alpha of .05/2=.025 and a power of 90%, PASS (Power Analysis & Sample Size, PASS 2022; NCSS, LLC [51]) software estimated the total sample size to be 77 for PROMIS S-E and 83 for SSMBT. However, the proposed model will have effects for time (0, 1, and 2), group (C-SCAT vs usual care), time-by-group interaction, site (1, 2, 3, 4, and 5), site-by-group interaction, and population (adolescent vs young adult). Accounting for the 16 degrees of freedom necessary to fit these model effects, the total sample size will be 83+16=99 who complete time 2. Allowing for an attrition as high as 20%, the final sample size will be 126 AYAs or approximately 25 per site. Recruitment in our preliminary multisite studies demonstrated that this sample size is feasible within the proposed period of the project.

Descriptive statistics will be computed for demographic and all outcome variables. All data will be examined graphically to determine the distributional properties. In cases of nonnormally distributed data, transformations may be used for analyses.

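### The set labelled intention-to-treat leaves out randomised participants who have only a baseline measure, although the planned mixed model can use them

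*Protocol article*

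**What the plan says.** The analysis set is defined in one sentence of the Missing Data section: "Following an intention-to-treat principle, participants with any postintervention data will be included in the analysis". The only other handling given there is for items: "We will use mean imputation for any missing data within a scale". No other analysis set is named for the primary outcomes.

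Three other statements bear on this rule:

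- Trial Design puts baseline before randomisation: "Time 0 (baseline, followed by randomization) occurs at or near the enrollment visit".
- Aims, under Data Analysis Plan, specifies "fixed effects for group (C-SCAT and UCCG), time (0, 1, and 2), group-by-time interaction", and adds: "This model will include a random effect for participant". Baseline is therefore a response, not a covariate.
- The primary test in the same section is made "using a contrast on the group-by-time interaction to specifically test for an immediate effect of C-SCAT versus the UCCG at time 1".

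On attrition, Sample Size and Power writes "Allowing for an attrition as high as 20" per cent and arrives at 126 participants from 99 who complete time 2. Description of the UCCG explains that staff contacts in usual care are meant partly to prevent disproportionate attrition in that arm. Randomization states that staff and participants are unblinded.

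**The concern.** Whether a participant supplies any postintervention data is known only after randomisation. A set defined by it is no longer the set that was randomised, so the intention-to-treat label does not fit.

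The rule also discards usable data. A participant randomised as planned has a time 0 value. In a likelihood-based mixed model with time 0 as a response, that value tells the model how the people lost before time 1 differed at the start. Under missing at random given baseline, this is the information that keeps the time 1 contrast unbiased. Without it, the baseline means come from a selected group, and the selection may differ between arms.

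At stake is the primary contrast for both co-primary outcomes, and an analysis reported under a name it does not meet.

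**Working it through.** **Number affected.** The plan's own figure first: 99 / (1 − 0.20) = 123.75, so 124, against 126 stated; this agrees within two participants. If all of the 20% were lost before time 1, 126 × 0.20 = 25.2, or about 25 participants, would be left out. The 99 are completers of time 2, so losses between times 1 and 2 count towards the 20% but remove nobody from the set. About 25 is therefore a ceiling at the planned attrition.

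**Formula.** I read the primary contrast as the difference between arms in change from time 0 to time 1. Let SD be the outcome standard deviation, ρ the correlation between time 0 and time 1, and m the mean baseline of those retained in an arm, in SD units above that of all randomised to it. Given baseline, expected change falls by (1 − ρ) per unit of baseline. In the restricted set:

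bias = −(1 − ρ) × SD × (m in C-SCAT − m in control).

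The bias is zero when m is equal in the two arms: either early loss is unrelated to baseline, or it is related in the same way and at the same rate in both.

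**Inputs from the article.** Effects of 10 (PROMIS S-E) and 4.8 (SSMBT); inflated residual figures 12.73 and 6.35; alpha 0.025 per outcome.

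**Assumptions not in the article.** The residual figures are used as total SDs; ρ is 0.3 to 0.7; all visits have equal correlation; dropout before time 1 is logistic in baseline, with log-odds changing by up to 1 per SD; tests are two-sided.

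**PROMIS S-E, low-baseline participants lost in the C-SCAT arm, random loss in control, equal rates:**

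| Lost before time 1 | Log-odds per SD | m in C-SCAT | ρ | Bias (points) |
|---|---|---|---|---|
| 20% | 1 | 0.173 | 0.3 | −0.7 × 12.73 × 0.173 = −1.54 |
| 20% | 1 | 0.173 | 0.5 | −0.5 × 12.73 × 0.173 = −1.10 |
| 20% | 1 | 0.173 | 0.7 | −0.3 × 12.73 × 0.173 = −0.66 |
| 10% | 1 | 0.091 | 0.5 | −0.5 × 12.73 × 0.091 = −0.58 |
| 10% | 0.5 | 0.049 | 0.5 | −0.5 × 12.73 × 0.049 = −0.31 |
| 5% | 1 | 0.047 | 0.5 | −0.5 × 12.73 × 0.047 = −0.30 |

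A simulation at the trial's size (63 per arm, 3000 runs per setting) gave −1.65, −1.11 and −0.72 for the first three rows. With the baseline-only records kept, the same settings gave −0.06, +0.03 and −0.05. Reversing the arms reverses the sign.

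**SSMBT, large-sample check (2,000,000 simulated participants, true effect 4.8, log-odds 1 per SD, ρ 0.3 to 0.7).** With all randomised kept, the contrast was recovered to within simulation error (4.79 to 4.82) in every scenario. With the restricted set:

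- same rate and same dependence in both arms: no bias;
- 10% versus 30% lost, same dependence: about −0.3 to −0.7;
- 20% lost in each arm, dependence in one arm only: about −0.3 to −0.8;
- opposite dependence in the two arms: about −0.7 to −1.5.

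**Against sampling error.** At ρ = 0.5 with about 50 analysed per arm, the standard error of the PROMIS S-E contrast is √(2 × 0.5 × 12.73² × 2/50) = 2.55. A bias of 1.1 is 0.43 of that and moves the nominal 0.025 test to about 0.039. At 10% loss (bias 0.58) it moves to about 0.029.

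**The case against.** The strongest reply is that the rule is milder than it looks.

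- **Any postintervention data means time 1 or time 2.** Someone with either visit stays in and keeps the model's handling of missing data. A reader might infer that the plan amounts to a completer comparison, or that it abandons the mixed model's protection. The text does not support that: only participants missing both visits are lost. This stands.
- **Size and direction are not established.** The 20% is an upper allowance running to time 2, and the dropout pattern is assumed. The practice session takes about 5 minutes and both arms have three staff contacts, so strong dependence in the C-SCAT arm alone is not obvious. The attrition the article itself worries about is in usual care. This stands, which is why the result is a range in either direction. The opposite-dependence pattern gives a larger shift, but nothing in the article points to it.
- **The sentence says who is included and does not literally exclude anyone.** True, but exclusion is its natural reading.

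A reader might also infer a further defect from "The time 1 visit for the C-SCAT group is scheduled" relative to completion of the intervention, namely that participants who stop early have no time 1 visit. The article does not say they go unfollowed. It offers telephone contact and an e-mailed link to those without a scheduled visit in the window, and follow-up after early stopping is commonly left to the full protocol. No finding rests on this.

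**Conclusion.** The point holds in a limited form. The sentence gives an intention-to-treat label to a set conditioned on a post-randomisation event, and it leaves out baseline-only participants whom the plan's own model can analyse. Both follow from the text without any numerical assumption.

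Whether bias follows depends on how early dropout behaves. For PROMIS S-E the range is 0 to about 1.6 points of the 10-point target. The top requires all 20% to be lost before time 1, a change of 1 in log-odds per SD of baseline in one arm only, and a correlation of 0.3. With 5% to 10% lost before time 1 at the same dependence and a correlation of 0.5, it is about 0.3 to 0.6 points, well under one standard error. The bias may favour either arm.

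This should be fixed, because the correction is simple and removes an avoidable risk. The documents do not show that the primary result would be materially wrong without it.

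**What to change.** Replace the sentence on the analysis set with one stating that all randomised participants with any observed outcome, including those with baseline only, are analysed in their assigned arm by likelihood in the planned mixed model, under missing at random. Keep the set with any postintervention data as a sensitivity analysis and label it modified intention-to-treat.

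The cost is one sentence in the analysis plan and one additional model fit per outcome. No new data, visits or staff are needed, and recruitment is expected to run to Fall 2026, so the change can be made before the analysis. It does not protect against dropout that is not at random.
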